### Step one: PMTCT cascade analysis to understand pMTCT performance, identify and prioritize areas for improvement

An essential step for systems improvement is to engage facility-level pMTCT staff and managers in understanding their system’s performance and using performance data to identify and prioritize areas for improvement. A pMTCT cascade analysis tool (PCAT) was developed to provide this systems view and highlight priority areas to address within the pMTCT cascade, based on a similar approach representing the linkage between HIV testing and combination antiretroviral services in Mozambique (Figure 4) [51]. This Microsoft Excel^©^-based tool uses routinely collected facility data to calculate the number and proportion of women and children flowing through each step of the pMTCT cascade, broken down into the flow from ANC through birth, and the subsequent postpartum period. The PCAT is also automated to calculate the number lost at each step (difference between those eligible for and those successfully passing through each step), and to estimate the additional number of women and exposed infants who would complete all pMTCT steps if each step were individually improved; this calculation assumes that drop-offs for all other steps remain constant and rates of eligibility to pass to next steps are similar among those who do and do not pass through each step. As the first step of the SAIA intervention, the cascade analysis tool is used by study personnel to guide a discussion with facility-level staff to determine which steps in the pMTCT cascade are likely to have the largest effect in order to optimize overall pMTCT services.

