### Step four: assess workflow modification effect on pMTCT cascade

Using routinely reported pMTCT cascade data from the pMTCT step that was selected for improvement, facility staff will monitor improvements in relevant indicators for two to six weeks following the introduction of the facility-specific workflow adaptation. Monitoring data will be analyzed visually and using descriptive statistics after a short time period, relying on improvements in the absolute increase in the proportion of women or infants successfully progressing through the step of interest to capture large, rapid improvements associated with the introduction of the adaptation.

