It is expected that each change cycle will require four to six weeks of testing to allow for sufficient time to detect desired effects on the pMTCT cascade, but to be short enough to allow for multiple iterations during the six-month intervention period. After each cycle, study staff will work with facility staff to review the original implementation plan, describe what actually occurred (including review of planned metrics to assess improvements), discuss what worked well and why, and identify what could be improved and how. The five-step SAIA intervention cycle will again be repeated to review PCAT data, update process maps, and develop the next change cycle. It is expected that between four and six change cycles will be implemented in each facility over the six-month intervention period.

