Descriptive analyses will include visual inspection of data for time trends across the study facilities, as well as within each facility, to identify trends, assess whether specific workflow adaptations led to improvements in the pMTCT cascade, and describe the sustainability of effects associated with individual adaptations. Those adaptations that are found to have dramatic or sustained effects will be documented as part of identifying best practices for pMTCT improvement. Exploratory bivariate analyses using student’s t-tests and chi-square tests will be carried out among facilities that showed large improvements in study outcomes during the six-month implementation period to identify descriptive factors that may be associated with adoption or may mediate the impact of the SAIA intervention.

Analysis of the implementation process data will include aggregate reporting of individual items from the Likert scales, as well as disaggregated analysis by study country, and by facilities found to have relatively better success with the intervention. The constant comparison method will be used to describe responses to qualitative data from open-ended questions, field diaries, and key informant interviews.

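### Adaptations may be listed as best practice on visual inspection, with no stated comparison role for control facilities and no need for the gain to last

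*Protocol article*

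**What the plan says.** The Analysis section describes trial-level descriptive work: time trends are inspected visually, across the study facilities and within each one. Among its purposes is to "assess whether specific workflow adaptations led to improvements in the pMTCT cascade". The consequence follows: "Those adaptations that are found to have dramatic or sustained effects will be documented as part of identifying best practices". Neither criterion is defined, and meeting either one is enough.

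Two parts of the intervention description bear on this. Under step one, a facility's own routine data go into the cascade tool, and a discussion with staff is meant to "determine which steps in the pMTCT cascade are likely to have the largest effect in order to optimize overall pMTCT services". The section on introducing the intervention says the tool is first filled with the most recent six months of that facility's data. Step four sets out the in-cycle check: "facility staff will monitor improvements in relevant indicators for two to six weeks following the introduction of the facility-specific workflow adaptation". That check uses plots and simple summaries, and its criterion is how many percentage points the targeted step has gained. The section on introducing the intervention gives a different window: "each change cycle will require four to six weeks of testing to allow for sufficient time to detect desired effects".

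**The concern.** The method (visual inspection), the purpose (a causal statement about one adaptation) and the consequence (a place among the best practices) are all fixed in the text, but nothing states what the series would have done without the adaptation. Three other explanations for a rise stay open:

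- **Chance.** Monthly facility proportions are noisy. The Study timeline section takes 12 months of baseline for that reason.
- **Regression to the mean.** A step prioritised because its recent figures looked poor will tend to look better next time.
- **Secular trend.** The Discussion reports rapid guideline change towards Option B/B+, which could raise ARV uptake whatever a facility changed.

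The Background criticises earlier quality-improvement evidence for lacking a counterfactual. At the level of the single adaptation, the plan does not say how it avoids the same weakness. The Discussion names identifying strategies for further testing and wider implementation as an intention of the trial, so what is at stake is a list other programmes may copy.

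**Working it through.** **The plan's own figures.** The Analysis text gives no number on this point. Table 4 concerns the primary comparison. A two-sample t-test on change scores (SD 11, two-sided α 0.05, power 0.80) gives 19.75, 13.16 and 10.57 points at 6, 12 and 18 per arm, against the stated 19.7, 13.2 and 10.6. Table 4 therefore reproduces and is not touched by this point.

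**Number of judgements.** 18 intervention facilities × 4 to 6 cycles = 72 to 108 adaptations.

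**Illustration under no true effect.**

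- From the article: a six-month baseline for choosing the step; a 50% level (the Sample size baseline for the ARV outcome); cycles of about four weeks; a 20-point rise as the meaning of dramatic, borrowed from the change predicted in the Sample size section because the Analysis section defines none.
- Assumed: *m* eligible women per facility-month; four candidate steps at the same true level; the lowest always chosen.
- Model: baseline = minimum of four Binomial(6*m*, 0.5)/6*m*; follow-up = a binomial proportion on *m* × weeks/4.345 women; count follow-up − baseline ≥ 0.20. 200,000 draws per setting.

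| *m* per month | Window | Rise ≥ 20 points |
|---|---|---|
| 5 | 4 weeks | 36% |
| 10 | 2 weeks | 27% |
| 10 | 4 weeks | 24% |
| 10 | 6 weeks | 18% |
| 20 | 4 weeks | 11% |
| 40 | 4 weeks | 3% |

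At *m* = 10 and four weeks: 72 × 0.238 = 17 and 108 × 0.238 = 26 spurious large rises. The mean spurious rise from selection is 6.6 points.

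**Sensitivity to the assumptions.**

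- With a step picked at random and one follow-up month, chance alone gives 13% at *m* = 10, 5% at 20 and 0.4% at 50.
- With the lowest of three equal steps, these become 21%, 9% and 0.9%.
- With four unequal steps (50, 60, 70, 80%), *m* = 10 and four weeks, the rate falls from 24% to 17% and the mean spurious rise from 6.6 to 1.9 points.

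**What a remedy must do** (four equal steps, *m* = 10, four weeks, three comparison facilities per stratum as the Randomization section implies).

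1. Subtracting comparison change alone: 24% becomes 26%. The comparison step was not selected for being low, so regression to the mean stays and some noise is added. At *m* = 20 the rate goes from 11% to 14%; at 40, from about 3% to 5%.
2. Under an assumed 10-point secular rise in both arms, the uncontrolled rate is 45% and the controlled rate 26%. Trend is what the subtraction removes.
3. Also requiring the controlled gain to be at least 20 points over the three post-intervention months brings the rate to about 5%.
4. Measuring from 12 months, of which six chose the step, halves the selection effect: 6.6/2 = 3.3 points. With items 1 and 3 the rate is then about 2% (6% at *m* = 5; 0.3% at *m* = 20).

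**The two windows.** Two to six weeks and four to six weeks overlap but have different lower ends, and the second is described as the time required to detect an effect.

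**The case against.** A reader might infer that best practices are declared from a few weeks' look by eye, with no comparison facility, so that many ineffective changes will certainly be listed. The documents do not support that reading:

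- The two-to-six-week look is in-cycle quality-improvement monitoring by facility staff, uses descriptive statistics as well as plots, and is part of the intervention under test. The best-practice sentence belongs to a separate trial-level analysis that also considers sustainability.
- Trends are inspected across the study facilities, and the Study facilities and setting section uses that term for both arms. Comparison series may therefore be looked at.
- The Discussion speaks of potential strategies for further testing, which is close to calling them candidates.
- Steps are not mechanically the minimum. The tool ranks them by estimated gain in full-cascade completion, and discussion, process maps and feasibility follow.
- Facilities were the largest 12 per country by first ANC visits, and the HIV-testing outcome has all first visits as denominator, so noise there may be small.

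All of this stands and limits the point. It does not remove it: inspecting all facilities is not the same as assigning the comparison arm a role, one dramatic rise is enough for listing, and the causal wording is stronger than that of the Discussion. Full definitions of the two criteria may sit in a document not shown, but the alternative between them is fixed here.

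It is also fair that adaptations may target steps outside the three primary outcomes (CD4 testing is an example in Table 1), for which comparison-arm data are not described, and that persistence cannot isolate one adaptation when further cycles follow in the same facility.

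**Conclusion.** The point holds as a weakness in an exploratory analysis. As written, the plan allows a chance rise, regression to the mean or a secular trend to be credited to an adaptation and listed as best practice, most plausibly where monthly denominators are small. It does not show that this will happen often. The illustrative rate runs from 36% at 5 women per month to 3% at 40, and depends on an assumed 20-point threshold, equal steps and always choosing the lowest. The randomised comparison and the sample size are unaffected. The change is a cheap improvement, worth making because the list is a stated product of the trial. The mismatch of windows is minor.

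**What to change.** In the Analysis section:

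1. For adaptations aimed at one of the three outcomes collected in both arms, report the change in the targeted indicator minus the change over the same calendar months in comparison facilities of the same country-by-volume stratum. Calendar alignment matters because introduction was sequential.
2. Measure that change from the full 12-month baseline, not only from the six months used to choose the step. This reduces regression to the mean, which subtraction of comparison change does not.
3. Replace the either-or rule by a single criterion: the gain over comparison persists through the three post-intervention months.
4. Report the number of adaptations tried beside the number retained.
5. Call the retained ones candidates for further testing, and state that later cycles in the same facility prevent clean attribution to any one of them. Describe adaptations aimed at other steps without an effect claim.

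Separately, reconcile the monitoring window under step four with the cycle length in the section on introducing the intervention.

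Cost: a little more descriptive analysis, on monthly data already planned for all 36 facilities, and fewer adaptations listed.

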### Trial design

This study employs a two-arm, 1:1 cluster randomized trial design to assess the effectiveness of the SAIA intervention. The unit of intervention is the health facility. A total of 36 health facilities are part of the trial, including 18 intervention and 18 comparison facilities (six intervention and six comparison facilities per country).

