### Covariates

Additional facility-level descriptive factors will be collected via interviews with facility managers and direct observation by trained study personnel using a data collection instrument designed for the purposes of this study. Covariates cover information on the facility (size, geographic location, public/non-profit managed), staffing levels and structure, service utilization, available auxiliary services (laboratory, pharmacy, community outreach), and other similar factors that may affect both the adoption and effects of the intervention.

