### Sample size

Sample size estimates are based on the health facility as the unit of analysis, and were calculated to detect the change in the proportion of HIV-infected pregnant women receiving antiretroviral medicines in pregnancy (arguably the most important endpoint of the study). Using program data from 2009 to 2010, we estimated a mean pre-intervention baseline of 50%, and predicted a mean post-intervention level of 70% for intervention facilities (mean change score = 20%) and 50% for control facilities (mean change score = 0%), and a standard deviation of yearly change scores of 11%. Assuming α = 0.05 and β = 0.80, the sample size is sufficient to detect an 11% and a 20% difference in mean change scores across the three countries and at the country level, respectively (Table 4).

**Table 4 T4:** Sample size and detectable change in study outcomes

**Sample size (Intervention: Control)**	**Detectable alternative in gain scores across intervention and control facilities**
6:6	19.7%
12:12	13.2%
18:18	10.6%

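### The exploratory tests of facility factors are confined to facilities that improved, which conditions on the outcome and names no comparison with facilities that did not improve

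*Protocol article*

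**What the plan says.** The protocol article, under Analysis, plans bivariate t-tests and chi-square tests labelled exploratory. It fixes their analysis set: "will be carried out among facilities that showed large improvements in study outcomes during the six-month implementation period to identify descriptive factors". It also states their purpose: "to identify descriptive factors that may be associated with adoption or may mediate the impact of the SAIA intervention". The sentence does not say which two groups each test compares, and it mentions no facilities with small or no improvement.

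Three other places bear on the point.

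- Under Data sources, Covariates, the article lists the facility characteristics to be collected, ending with "other similar factors that may affect both the adoption and effects of the intervention". Nothing there limits collection to improving facilities.
- The next paragraph of the Analysis section breaks down the Likert process items: "disaggregated analysis by study country, and by facilities found to have relatively better success with the intervention". This is reporting of process items, separate from the tests of facility factors.
- Under Trial design: "A total of 36 health facilities are part of the trial, including 18 intervention and 18 comparison facilities".

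**The concern.** To learn whether a characteristic goes with success, one has to see how common it is, or how high it runs, in facilities that succeeded and in those that did not. A set restricted to successes gives only the first half of that comparison. If improvement is treated as yes or no, every facility in the set is a yes, and a table of factor by improvement has an empty row. What remains is variation in the size of the gain, or in adoption, among facilities already selected for a large gain. That selection has removed much of the variation that a real factor would have produced.

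At stake is the trial's attempt to say which facility characteristics go with adoption or impact. Followed literally, the plan would probably miss factors of substantial size and could lead the authors to report that nothing was associated with success. The estimate of the intervention's effect is not at stake.

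**Working it through.** **Inputs from the protocol article**

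- 18 intervention facilities (Trial design).
- "a standard deviation of yearly change scores of 11" percentage points, and an expected mean gain of 20 points (50% to 70%) in intervention facilities (Sample size).
- Alpha 0.05, taken as two-sided, and power 0.80 (printed as β).

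**The plan's own figures first.** The sentence at issue carries no number. The only sample-size figures are those of Table 4, and they confirm how the SD of 11 is used. For a two-sample t-test with n per arm, the noncentrality is δ / (11 × √(2/n)) on 2n − 2 degrees of freedom. Solving for 80% power:

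| n per arm | Table 4 | Recomputed |
|---|---|---|
| 6 | 19.7 | 19.75 |
| 12 | 13.2 | 13.16 |
| 18 | 10.6 | 10.57 |

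Table 4 reproduces.

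**Assumptions not in the documents**

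- A binary factor is present in 9 of the 18 intervention facilities.
- It shifts gain by D = 10, 15 or 20 points.
- 'Large improvement' means the top 9 of 18, with the top 6 as a stricter variant.
- The SD of 11 applies within each factor group. The protocol gives it for yearly change in the antiretroviral outcome, so using it for six-month change, or for the other two outcomes, is an extrapolation.

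**Model.** Gain = 20 + D × (F − 0.5) + normal error with SD 11, where F is 0 or 1. Each of 8,000 simulated trials ranks the 18 facilities by gain. A t-test of gain by factor is then run in all 18, in the top 9 and in the top 6.

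**Analytic check for all 18.** The noncentrality is D / (11 × √(2/9)), which is 1.93, 2.89 and 3.86 for D = 10, 15 and 20. With 16 degrees of freedom and a critical value of 2.12, power is 44%, 78% and 95%, as in the simulation.

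| True shift D | All 18: mean difference, power | Top 9: mean difference, power | Top 9: no test possible | Top 6: power | Top 6: no test possible |
|---|---|---|---|---|---|
| 0 | 0.1, 5.3% | 0.0, 5.0% | 0.3% | 4.2% | 14% |
| 10 | 10.0, 44% | 4.0, 6.8% | 7% | 2.9% | 50% |
| 15 | 15.0, 78% | 5.9, 6.9% | 24% | 1.6% | 76% |
| 20 | 20.0, 95% | 8.1, 7.1% | 48% | 0.5% | 92% |

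'No test possible' means that one factor group has fewer than two facilities left. Those runs count as non-significant in the power column, and the mean difference is taken over the remaining runs. Counting only runs where the test can be done, power in the top 9 is 6.8/0.931 = 7%, 6.9/0.761 = 9% and 7.1/0.518 = 14%. The conclusion does not depend on that convention.

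**The contrast that is given up.** In the same simulations the factor is present in 68%, 76% and 82% of the top 9, against 32%, 24% and 18% of the bottom 9. Looking only at the top 9 gives the first set of percentages with nothing to set them against.

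**What a two-group comparison could detect.** With 18 intervention facilities, splits of improvers to others of 9:9, 6:12 and 4:14 detect standardised differences of 1.41, 1.49 and 1.69 at 80% power. Even the repaired analysis finds only large differences.

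**The case against.** **The authors may have meant improvers against the rest.** A t-test or chi-square test needs two groups, the Likert paragraph speaks of relatively better success, and the covariates are not restricted to improvers. This reading is quite possible. But the sentence restricts the set and names no second group, and nothing elsewhere in the article supplies one for these tests. If that was the intention, the wording needs correcting all the same.

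**The analysis is exploratory.** True, and this limits how much weight the point deserves. The label tempers the claims that can be made, but it does not provide the missing comparison.

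**An association is not impossible among improvers.** This stands. Gain still varies among them, and an attenuated effect of 4 to 8 points remains. The loss is one of size and power.

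**Two stronger readings are tempting and should be resisted.**

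- A reader might infer that this is the only quantitative look at where the intervention works. It is not. The Analysis section also plans sub-analyses by country and facility size, and the Likert breakdown.
- A reader might infer that traits shared by every facility would emerge as drivers of success. A trait without variation cannot be tested, and with no true effect the rejection rate among the top 9 stays at 5%.

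**The missing cut-off and the time window.** A definition of large improvement may well sit in a fuller analysis plan, and its absence from an article is not a fault. The implementation months are a reasonable window for a question about adoption, which happens in those months.

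**Conclusion.** The point holds in a limited form. As printed, the sentence selects facilities on the outcome and names no facilities without improvement as comparator. Under the stated assumptions, a factor worth 10 to 20 points would appear as about 4 to 8 points in the best-improving half, with power near 7%, against 44% to 95% if all 18 intervention facilities were used.

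The SD and mean gain are the protocol's own. The factor's prevalence, its effect and the cut for large improvement are assumptions, so the figures show the order of the loss and do not predict it exactly. The harm is attenuation and lost power, not false positives. The primary t-tests and the secondary segmented regression are untouched. The sentence should be corrected, but the point does not threaten the trial's main conclusion.

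**What to change.** Reword the sentence so that the exploratory analysis covers all 18 intervention facilities. Either relate each factor to the continuous change score, by regression or rank correlation, or compare facilities with large improvement with those without it, defining 'large' beforehand. For factors measured in both arms, add an analysis of all 36 facilities with a factor-by-arm term. This addresses whether the factor modifies the intervention's effect, as opposed to going with change in either arm. The implementation-period window may stay for the adoption question. Keep the exploratory label, and say that only large associations can be found with 18 facilities.

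The cost is a change of wording and a little more analysis. No additional facilities or instruments are needed, because the planned covariate collection is not limited to improving facilities.
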